### Quantitative Methods

To collect the quantitative data, we use paper-and-pencil and electronic versions of the questionnaires. Those in the active intervention groups fill out the questionnaires before or after the intervention sessions if the questionnaires are provided electronically and during the session if the questionnaires are provided on paper. Those in the no-intervention group fill out the questionnaires based on the email reminders of the electronic data collection system (time interval between reminders is the same as the interval between sessions in the active intervention groups).

Electronic data collection is implemented in the Research Electronic Data Capture (REDCap) system (Vanderbilt University) [41], provided by the UH for collecting sensitive research data electronically. In the case of the TBWS intervention, data collection from time points before and immediately after the intervention is partly integrated into the online course platform, and the students can respond either via the course platform or via the REDCap system, while data collection from week 3 and the 1- and 3-month follow-ups is implemented only in the REDCap.

Before the analysis phase, the data validity is confirmed via range checks, missing value checks, and outlier detection. Potentially erroneous data are checked against the paper and electronic forms, and other necessary sources, and corrected if needed. All modifications are documented.

Participant retention is promoted by reminding the participants during the group meetings to fill out the questionnaires. All participants receive up to 5 reminder messages from the electronic data collection system if they do not complete the necessary questionnaires on time. Retention is also promoted by the possibility of receiving written feedback on the questionnaire results after participation. Participating students also receive movie tickets as compensation for completing all follow-up questionnaires. Adherence to the G4H intervention is monitored by documenting the number of sessions in which each student participated.

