### Statistical Analyses

We will conduct our analysis following the intention-to-treat principle, including all participants regardless of whether they completed the intervention.

The change in the outcome variables over time will be analyzed with linear mixed-model analyses due to the hierarchical data structure. Information criteria are used to assess model fit and determine the appropriate model structure. Mixed effects models can also be fitted for participants with missing data from one or more time points. If needed, other appropriate imputation methods, such as multivariate imputation by chained equations [63], will be used. For this reason, the number of participants included in the analyses is likely to be higher than the number of participants providing data at the last follow-up.

We will explore with logistic regression analyses whether background characteristics and baseline psychiatric symptoms predict study dropout, and necessary means to account for any systematically missing data will be taken. We aim to show that the missing observations of the outcome variable, due to dropout, are conditionally independent from the observed values of the outcome variable given our model for dropping out from the study. If needed, inverse propensity score weighting is carried out so that the treatment effects are conditionally independent from the treatment group assignments and from differing dropout rates given the propensity scores. We consider individuals’ selection into different study groups (arms) under the stable unit treatment value assumption based on their background characteristics, given that we have access to an extensive dataset. The selection of individuals into groups is accounted for by making the estimators double robust, which is a well-known approach to adjust for selection into groups based on background characteristics in model-based estimates [64,65]. This ensures that our results are unbiased and consistent estimators of the treatment effects. Potential effects of the COVID-19 pandemic on the stability and change in students’ well-being will be inspected and considered in the analyses if necessary.

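### Course stopping is recorded only for G4H and is not a named dropout predictor, although week-7 response in the active arms may depend on it

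*Protocol article*

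**What the plan says.** **Analysis (Statistical Analyses).** The analysis follows the intention-to-treat principle, "including all participants regardless of whether they completed the intervention". Outcomes go into linear mixed models, and "Mixed effects models can also be fitted for participants with missing data from one or more time points"; imputation by chained equations is available if needed. On dropout the section says "We will explore with logistic regression analyses whether background characteristics and baseline psychiatric symptoms predict study dropout", and adds that "necessary means to account for any systematically missing data will be taken". It then sets itself the aim of showing that outcomes missing through dropout are conditionally independent of the outcome given the dropout model, with inverse propensity weighting if needed.

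**Collection (Quantitative Methods).** "Those in the active intervention groups fill out the questionnaires before or after the intervention sessions if the questionnaires are provided electronically"; paper forms are completed in the session itself. "Participant retention is promoted by reminding the participants during the group meetings to fill out the questionnaires". For TBWS, "data collection from time points before and immediately after the intervention is partly integrated into the online course platform", with REDCap as the alternative at those two points and the only route at week 3 and both follow-ups. Controls answer from e-mail reminders. Everyone can receive up to five electronic reminders.

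**Adherence.** "Adherence to the G4H intervention is monitored by documenting the number of sessions in which each student participated". Table 1 lists attendance for arm 1 only, and no equivalent is listed for SPGs or TBWS.

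**Attrition (Results).** Attrition passed the anticipated 35% in SPGs and TBWS. The low TBWS response at week 3 is put down to that survey being in REDCap only and not on the course platform.

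**The concern.** A student who stops a course loses the in-course routes to the questionnaire: the session, the facilitator's reminder or the course platform. A control has no such route to lose. Stopping may therefore lower response in arms 1 to 3 only, and it may also go with smaller benefit. A dropout model built from background and baseline symptoms cannot make missingness independent of outcome when a post-baseline event drives both. The event is also not recorded in the two arms where attrition ran above plan. If both links hold, the week-7 estimate moves toward the effect in completers while keeping the intention-to-treat label. Comparisons of G4H with SPGs and TBWS could be affected too, because the collection routes differ between the active arms.

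**Working it through.** **The plan's nearest figure.** The document gives no number for this bias. Its 35% attrition enters only the power statement. With N = 600 × 0.65 = 390, f = 0.20 and four arms, and assuming m = 4 measurements, correlation 0.5 and alpha = 0.05/6, the noncentrality is f²Nm/(1+(m−1)ρ) = 0.04 × 390 × 4/2.5 = 24.96. With 3 and 386 degrees of freedom, power is 96.2%. The stated figure of at least 95% thus reproduces under these assumptions (90.1% if the correlation is 0.7). That treats attrition as lost precision and says nothing about selective loss.

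**Inputs for the bias, all assumed.** The documents give no completion rate, no response by completion status and no effect in stoppers. Let s be the share who stop, response be r_c = 0.80 in completers and r_s in stoppers, and the effect be d_c = 0.30 SD in completers and d_s in stoppers. Control nonresponse is taken as uninformative.

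- True effect = (1−s)d_c + s·d_s
- Observed effect = [(1−s)r_c·d_c + s·r_s·d_s] / [(1−s)r_c + s·r_s]

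Example with s = 0.3, r_s = 0.3, d_s = 0: true = 0.7 × 0.30 = 0.210; observed = (0.7 × 0.8 × 0.30)/(0.56 + 0.09) = 0.168/0.65 = 0.258, which is 23% too large.

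| s | r_s | d_s = 0: true → observed | Overstated | d_s = 0.15: true → observed | Overstated |
|---|---|---|---|---|---|
| 0.2 | 0.8 | 0.240 → 0.240 | 0% | 0.270 → 0.270 | 0% |
| 0.2 | 0.6 | 0.240 → 0.253 | 5% | 0.270 → 0.276 | 2% |
| 0.2 | 0.3 | 0.240 → 0.274 | 14% | 0.270 → 0.287 | 6% |
| 0.3 | 0.6 | 0.210 → 0.227 | 8% | 0.255 → 0.264 | 3% |
| 0.3 | 0.3 | 0.210 → 0.258 | 23% | 0.255 → 0.279 | 10% |
| 0.4 | 0.6 | 0.180 → 0.200 | 11% | 0.240 → 0.250 | 4% |
| 0.4 | 0.3 | 0.180 → 0.240 | 33% | 0.240 → 0.270 | 12% (12.5% unrounded) |

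The attrition rate alone does not say which row applies. The row with s = 0.3 and r_s = 0.3 gives 35% attrition, but so would 65% response in completers and stoppers alike, with no bias.

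**A second set of assumptions.** With 71% completing, response 85% against 35%, and effect 0.40 SD against 0: 0.40 × 0.6035/(0.6035 + 0.1015) = 0.342 against a true 0.284, about +21%. Raising stoppers' response to 65% gives about +7%. Keeping 35% but giving stoppers half the benefit gives about +9%.

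**Does using week-3 scores repair it?** A simulation with s = 0.3, r_s = 0.3 and d_s = 0 (true 0.210) gave 0.259 adjusting for baseline, 0.249 adding a week-3 outcome seen for everyone, and 0.210 with stopping in the model. Week 3 removed (0.259 − 0.249)/(0.259 − 0.210), about a fifth of the bias. In the trial it may remove less: Table 1 has no week-3 PHQ-9, only the four-item loneliness scale is repeated then, and TBWS response at week 3 was low.

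**The case against.** Collection is not wholly tied to staying in a course. Every participant can get up to five electronic reminders, surveys go out whether or not earlier ones were answered, electronic forms in the active arms are completed outside the session, and TBWS students may use REDCap at weeks 1 and 7. A reader might infer that the tie reaches the follow-ups. It does not: TBWS week 3 and both follow-ups are REDCap-only, and no follow-up is linked to sessions in any arm. All of this stands and confines the concern mainly to week 7, with week 3 in G4H and SPGs.

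A reader might also infer that the whole missing-data approach rests on pre-treatment variables. That describes the dropout regression only. The mixed model and any imputation use observed post-baseline scores, and further means are promised, though none is named. This softens the point without removing it, as the simulation shows. Background data include treatment motivation and readiness, which may predict stopping and were not in the simulation.

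The Strengths and Limitations section already names mode effects and structural missingness and promises sensitivity analyses, but it does not mention course stopping. A full list of auxiliary variables could fairly be left to an analysis plan that is not shown. An attendance record that was never gathered could not: it has to be retrieved.

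Finally, the low TBWS week-3 response is attributed to the survey channel, not to students stopping. It shows that channel matters for response, not that stoppers went missing.

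**Conclusion.** The point holds in conditional form. The named dropout predictors cannot support the conditional independence that the section aims to show if course stopping affects both response and benefit. Stopping is documented in one active arm of three, and not in the two where attrition exceeded 35%. The stronger statement, that the estimates do lean toward completers, is not supported: it needs stoppers to respond less and to benefit less, and the documents report neither. Students may also stop for reasons unrelated to benefit, and nonresponse among controls may be selective too. Under the assumed inputs the overstatement is 0% with equal response, roughly 2 to 12% if stoppers keep half the benefit, and 5 to 33% if they gain nothing. This is worth correcting before the RQ1 and RQ3 analyses, but it does not invalidate the design.

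**What to change.** 1. Derive a stopping or completion indicator in all three active arms from existing sources: G4H attendance, SPG attendance lists where they exist, and TBWS platform activity or course credit (completion earns 3 ECTS). Record it prospectively while recruitment for RQ4 continues.
2. Add it, with week-3 loneliness, group memberships and mood and the collection channel, to the dropout weights and the imputation model. These are auxiliary variables only; they must not become covariates of the treatment effect. Since controls cannot stop a course, fit these models by arm.
3. Add a sensitivity analysis in which outcomes are missing not at random among stoppers, and report response by stopping status in each active arm.

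No new survey route is needed, because electronic surveys and reminders already go to everyone. The cost is analysis-plan wording and retrieval of records from the course organisers. The downsides are somewhat more complex weights and possibly incomplete older SPG records.

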### Attrition

Figure 3 illustrates the attrition rates by trial arms by the first data freeze in March 2025. The percentages do not accurately indicate the number of study dropouts, as all surveys are sent to participants regardless of nonresponse to previous surveys, allowing them to re-enter the study. The attrition rate has exceeded the anticipated 35% in the SPGs and TBWS. For the TBWS, the bars with black outlines represent the responses to the REDCap survey. The low response rate at the week 3 assessment (during intervention) is due to the survey only being available in REDCap and not integrated into the online course platform as in week 1 and week 7. Based on the attrition rate, we took action to increase retention, including adding incentives for the participants (a movie ticket for completing the surveys).

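### The plan sets out to show a dropout condition that is misstated and that the collected data cannot establish, while attrition exceeds the planned 35% in both active comparators

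*Protocol article*

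**What the plan says.** All of the following is in the Statistical Analyses section of the protocol article unless noted.

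- **Aim on dropout:** "We aim to show that the missing observations of the outcome variable, due to dropout, are conditionally independent from the observed values", and the sentence continues "of the outcome variable given our model for dropping out from the study".
- **Dropout model:** logistic regression will explore "whether background characteristics and baseline psychiatric symptoms predict study dropout". Arm, survey mode and post-baseline outcomes are not named as predictors.
- **Remedies:** linear mixed models that keep participants with incomplete follow-up; "If needed, other appropriate imputation methods, such as multivariate imputation by chained equations [63], will be used"; "If needed, inverse propensity score weighting is carried out so that the treatment effects are conditionally independent", which the text links both to arm membership and to differing dropout rates; and the general promise that "necessary means to account for any systematically missing data will be taken".
- **Certainty claimed:** after describing double robust estimation for selection into arms, the section concludes: "This ensures that our results are unbiased and consistent estimators of the treatment effects".
- **Attrition so far (Results, Attrition):** "The attrition rate has exceeded the anticipated 35% in the SPGs and TBWS". The same paragraph warns that the percentages are not true dropout counts, because non-responders still receive later surveys and can come back.
- **Sensitivity analyses:** Strengths and Limitations promises them for differences between comparators, collection mode and structural missingness. The Cost-Effectiveness section promises one-way analyses of the economic results. Neither names dropout.

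**The concern.** Every dropout remedy that the article names is valid only if data are missing at random: given arm, covariates and the outcomes already seen, the probability of not responding must not depend on the outcome that was not seen. The article states a relation between missing values and observed values instead, and treats it as something the team can demonstrate. An assumption about values nobody recorded cannot be demonstrated from those that were recorded.

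The practical risk is false reassurance. If the regression on background and baseline symptoms finds little, the text invites the reader to treat dropout as harmless, and weighting and further imputation apply only if needed. The two arms reported above 35% are the active comparators in the hypothesis that G4H reduces loneliness for longer than the other interventions (Aim and Objectives). Follow-up response therefore matters most for that contrast.

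**Working it through.** **1. The plan's own figure involving attrition.** Sample Size gives at least 95% power at f = 0.20 with 600 recruited and 35% attrition. N = 600 × 0.65 = 390. Alpha, correlation, number of measurements and multiplicity rule are not stated. Assuming a four-arm repeated-measures ANOVA between-groups test with correlation 0.5, four measurements and alpha 0.05/6, power is 0.962, so the figure reproduces under those choices. The present point takes nothing from it: power concerns precision, and this point concerns bias.

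**2. Is the stated condition the one required?** Let R be the response indicator, Y_obs the outcomes seen and Y_mis those not seen.

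- Required (missing at random): R independent of Y_mis, given Y_obs, arm and covariates.
- Stated: Y_mis independent of Y_obs, given the dropout model.

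The second can fail when dropout is harmless. One baseline and one later outcome were simulated (correlation 0.6 assumed, n = 400,000). With dropout completely at random, missing outcomes correlated 0.60 with observed baseline. With dropout depending on baseline only, the figure was 0.59. In both cases imputation and weighting recovered the true mean.

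Those correlations do not condition on a dropout model. Conditioning on baseline removes the link with baseline but not with later observed scores. If every pair of time points correlates 0.6, the partial correlation of a missing 3-month score with an observed week-7 score, given baseline, is (0.6 − 0.6 × 0.6)/(1 − 0.6²) = 0.24/0.64 = 0.375, even under completely random dropout. So the qualifier does not turn the sentence into missing at random.

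**3. Can the dropout regression show ignorability?** In the same simulation, dropout was regressed on baseline:

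| Dropout depends on | Missing | Baseline coefficient | Bias, imputed mean | Bias, weighted mean |
|---|---|---|---|---|
| Baseline only | 39.5% | 0.493 | 0.00 | 0.00 |
| The outcome itself | 39.5% | 0.286 | −0.12 SD | −0.12 SD |
| Only the part baseline does not predict | 39.4% | 0.000 | −0.12 SD | −0.12 SD |
| The outcome itself, less dropout | 19.3% | 0.285 | −0.06 SD | −0.06 SD |

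The regression gave its cleanest result in a biased case and its strongest association in the harmless case. It describes who leaves; it does not test the assumption.

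**4. Size in a between-arm contrast.** Bias in an arm mean = fraction missing × departure of non-responders from the model's prediction. Assume 40% and 25% missing and a 0.3 SD departure; none of these is in the documents.

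- Same departure in both arms: (0.40 − 0.25) × 0.3 = 0.045 SD.
- Departure only in the 40% arm: 0.40 × 0.3 = 0.12 SD.
- Near-equal loss (35% and 36%), same departure even at 0.8 SD: 0.01 × 0.8 = 0.008 SD.

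For scale, f = 0.20 corresponds to d = 0.40 for two groups, so the first two are 0.045/0.40 = 11% and 0.12/0.40 = 30% of it.

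**5. What the article shows about unequal attrition.** Missing Values Analyses counts 2317 surveys over the four main time points. If everyone returned baseline, mean post-baseline response is (2317 − 699)/(3 × 699) = 77%, or (2317 − 732)/(3 × 732) = 72% with the 732 background responses as denominator. That is 23% to 28% missing on average. Arms above 35% therefore imply unequal loss across arms or time points, but the rates themselves cannot be recovered.

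**The case against.** The fair case for the plan is that this is one clumsy sentence in a condensed article. Read with its qualifier, it can be taken to mean that missing and observed outcomes share a distribution once dropout predictors are accounted for, which is the right intent. The regression is exploratory. The primary mixed model already uses arm and each participant's observed outcomes, so their absence from that regression does not remove them from the main analysis. Weighting for differing dropout and imputation are both provided for.

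Most of that stands as a limit on the point. It does not rescue the sentence: the charitable version is equally untestable, and the article still says it aims to show it.

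Stronger readings are tempting, and the documents do not support them:

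- *Attrition is never stress-tested.* Dropout modelling, weighting and imputation are planned, and an analysis for data missing not at random may sit in an analysis plan that is not shown. Its absence from the article is not a finding.
- *A null regression would be reported as proof that attrition is harmless.* The wording invites this, but no text says so.
- *The 3-month contrast is biased.* That needs dropout related to unseen outcomes, which nothing in the article demonstrates. The article also does not say at which time point 35% was exceeded, and participants can re-enter.

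**Conclusion.** The point holds as a defect in what is written. The condition is not the one the named methods rely on, the collected data cannot establish either version, and a baseline-only dropout regression cannot support ignorability. The statement that estimates are unbiased and consistent is attached to selection into arms, but it covers the treatment effects as a whole. It therefore needs the dropout assumption as well as correct selection modelling, and should be conditional on both.

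It matters because reported attrition exceeds the planned 35% in both active comparators. Any size is illustrative: 0.045 to 0.12 SD under the assumed 40% against 25% missing and 0.3 SD departure, and close to zero if loss and departure are similar in both arms. The conclusion about the wording rests on none of these assumptions.

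**What to change.** 1. Replace the sentence in Statistical Analyses with: *We assume outcomes are missing at random given arm, baseline covariates and previously observed outcomes; this cannot be verified from the data.* Keep the logistic regression as a description of who drops out.
2. Restrict the claim of unbiased and consistent estimation to hold under the stated assumptions.
3. Include arm, the latest observed outcome and survey mode in any dropout-weighting or imputation model. Mode has a stated reason: the TBWS week-3 and follow-up surveys are in REDCap only (Quantitative Methods), and the article attributes the low TBWS week-3 response to that restriction.
4. Extend the sensitivity analyses promised in Strengths and Limitations to dropout, for example a delta-adjusted analysis of ULS-8 and PHQ-9 at 3 months with delta allowed to differ by arm. Fix and justify the range of delta before outcome data are analysed.

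The cost is two edited sentences and a modest amount of extra analysis on data already being collected. The drawback is a less favourable statement of certainty.

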#### Arm 4: The No-Intervention Control Group

The control group consists of students who are currently not taking part in any group interventions for study skills or psychological well-being at the UH. The participants in the control group may, however, take part in other social and mental health services than those provided by the UH, and this is not restricted during their participation in the study. The recruitment and data collection among the control group are scheduled to take place simultaneously with the active intervention groups: the participants are recruited at the same time, and they answer the questionnaires at the same pace as the active interventions progress during the academic year.

The interventions studied in this protocol have been developed for educational contexts and thus are expected to be well-suited for the university context. As discussed earlier, the G4H builds on SIAH and SIMIC, particularly aiming at supporting well-being during transitions in life, such as entering a university [21]. In addition, both the SPGs and the TBWS courses have been specifically developed by experts within the UH for supporting university students’ well-being and academic ability.

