### Participants

#### Setting and Timeline

The study is conducted in an academic setting among UH students in Finland. The recruitment has progressed as follows: for the RQ1-RQ3, the recruitment for the first data freeze ended at the end of 2024, and for RQ5, the recruitment ends by the end of the year 2025. For the more explorative objective 2 (RQ4) on the factors that mediate or moderate intervention effectiveness, we assume that a larger sample is required, and recruitment continues longer (current ethical approval allows data collection until the end of 2028). We completed the first data freeze in March 2025 for the RQ1 to RQ3 and will complete the data collection of the qualitative data for the RQ5 by December 2026.

The quantitative data collection started in March 2022 for the G4H and the SPGs. From October 2022, the data collection from all 3 interventions and the no-intervention control group has taken place simultaneously. The intervention schedule and points of assessment are illustrated in Figure 1. It should be noted that data on health care and social service use, as well as the participants’ minority status and readiness to attend the intervention, were gathered only from students who participated starting from March 2023 for the no-intervention control group and from September 2023 for the active intervention arms. The research ethics committee was informed about these added outcome measures, and a new ethical approval was obtained from the committee before data collection started.

In the collection of qualitative data, participant observation is conducted in the meetings of the G4H group and interviews with facilitators (n=9) and intervention participants (n=11) at the end of the intervention period. In addition, the follow-up interviews with intervention participants will be conducted 12 months after the first interview (2024‐2026). Additionally, focus groups with young people belonging to minorities (n=19 participants) are arranged to discuss G4H in terms of equality and inclusion during the data collection period (2023‐2025).

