#### Recruitment

The UH student well-being services are available to all students at the university, and there are no exclusion criteria for the study. All the students willing to participate are included regardless of their level of loneliness, state of psychological well-being, or stage of studies. Students are recruited for the active intervention groups and no-intervention group by email, website, and social media advertisements circulated by the UH media and communications services, communications services at the faculties, student health services, and student organizations. The students are not randomly assigned to the intervention groups and can sign up for a course of their choice. The facilitators of the G4H intervention are also invited to participate in the study during the G4H facilitator training. All facilitators willing to participate are included in the study. Taking part in relevant concomitant care is not prohibited during the intervention study. The participating students or facilitators are not blinded to the study protocol.

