Furthermore, the lack of exclusion criteria and the nonrandomized design of the protocol may introduce potential biases regarding group composition. However, allowing students to choose which intervention they participate in respects their autonomy and aligns with ethical research practices. This nonrandomized design increases the ecological validity of our findings by capturing the experiences of students in a real-world educational environment, which is important for making informed decisions that can improve services at both individual and population levels [80]. Ecological validity was further increased by including all students in the interventions and in the study. We will implement strategies to address potential selection bias, including collecting detailed demographic and baseline data and using inverse propensity score weighting using double robust estimators, if necessary.

Due to the absence of comparable previous research with the same study population, a priori sample size calculations were not conducted. This represents a limitation, as underpowered samples may fail to detect treatment effects, while overpowered samples may lead to unnecessary use of resources. Nonetheless, the existing literature indicates that significant treatment effects can be observed with smaller sample sizes in different populations [17,24]. Given the complexity of our analysis plan, which includes mixed model analyses and potential (double robust) inverse propensity score weighting, we believe it was justified to aim for a larger target sample size in this study.

We did not appoint an independent data monitoring committee, as this is a naturalistic trial without randomization, and it investigates interventions that focus on psychosocial well-being rather than alleviating psychiatric pathologies. Moreover, there were no clinical inclusion criteria, and as the participants were university students, most showed rather low levels of psychological distress. Therefore, we anticipated minimal risk of harm from the interventions, a decision that was also accepted by the ethical review board of the study. However, we recognize that the presence of such a committee could have enhanced the integrity and trustworthiness of the data collection process.

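### The plan says double-robust adjustment guarantees unbiased effects in a self-selected four-arm study, and is inconsistent on whether that adjustment will be done

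*Protocol article*

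**What the plan says.** Allocation is by choice (Recruitment): "The students are not randomly assigned to the intervention groups and can sign up for a course of their choice".

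The Statistical Analyses section makes three statements about selection.
- Weighting is conditional: "If needed, inverse propensity score weighting is carried out so that the treatment effects are conditionally independent from the treatment group assignments".
- Double-robust estimation is presented without condition, as an approach to "adjust for selection into groups based on background characteristics in model-based estimates".
- The paragraph then concludes: "This ensures that our results are unbiased and consistent estimators of the treatment effects". The only identifying assumption it names for selection is the stable unit treatment value assumption.

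Strengths and Limitations describes the remedy for selection bias differently: "using inverse propensity score weighting using double robust estimators, if necessary".

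For dropout, Statistical Analyses names more predictors than it does for selection: "We will explore with logistic regression analyses whether background characteristics and baseline psychiatric symptoms predict study dropout".

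On timing, the section on Arm 4 says of controls and active arms that "the participants are recruited at the same time". Setting and Timeline says: "The quantitative data collection started in March 2022 for the G4H and the SPGs". It adds that all four arms ran together only from October 2022.

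**The concern.** In a non-randomised comparison, every effect estimate for RQ1 depends on how selection into arms is handled. The plan has three weaknesses here.

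First, it treats double robustness as a guarantee. The property protects against misspecifying one of two working models, given the covariates used. It does nothing about a cause of arm choice that is not measured or not included, or about students who have no counterpart in another arm.

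Secondly, a reader cannot tell whether the primary estimate will be adjusted. The data for RQ1 to RQ3 were frozen in March 2025 and registration was retrospective, so an open condition leaves the analyst a choice between estimates.

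Thirdly, the wording for selection is narrower than the wording for dropout in the same paragraph, and it does not mention enrolment period. G4H addresses social group memberships, whereas SPG themes are study problems such as attention and writing. Baseline loneliness and mood are therefore plausible drivers of arm choice.

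**Working it through.** **1. Does the guarantee hold?** A double-robust estimator is consistent if (a) there is no unmeasured confounding given the covariates, (b) arms overlap on them, and (c) the propensity model or the outcome model is correct. Even then the property is consistency, not exact unbiasedness in a finite sample. The text states none of (a) to (c) as a condition. Evidence in the document bearing on (a) and (b):
- Treatment motivation is collected in arms 1-3 only (Table 1).
- Readiness and minority status were gathered from March 2023 in controls and September 2023 in the active arms (Setting and Timeline). They are missing for earlier participants.
- Study years range from 0 to 8 in G4H and from 0 to 23 in SPGs (Table 2), so overlap is not assured.

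**2. Is the condition for adjusting already met?** The document's own tests, recomputed from the Table 2 counts, give chi-square (6 df) 15.8 for relationship status and 12.6 for living situation, as printed. Gender gives 25.4 (P=.0003). The text prints 5.4, which would give P=.49, so the printed P<.001 agrees with 25.4.

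Standardised difference = difference / square root of the mean of the two variances:
- Study years, G4H versus SPGs: (1.9 - 4.6) / √((1.6² + 3.7²)/2) = -2.7 / 2.85 = **-0.95**.
- Age, G4H versus controls: (27.4 - 25.1) / √((8.0² + 6.6²)/2) = 2.3 / 7.33 = **0.31**.
- Women, G4H versus controls: 110/154 = 0.714 and 175/203 = 0.862; -0.148 / √((0.204 + 0.119)/2) = **-0.37**.

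The Abstract and Participant Descriptive Statistics both conclude that group selection bias needs to be addressed.

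**3. Is adjustment planned or optional?**

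| Place | Weighting | Double-robust estimator |
|---|---|---|
| Statistical Analyses | conditional, no trigger | unconditional |
| Strengths and Limitations | conditional, no trigger | conditional, no trigger |

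These cannot all describe one primary analysis.

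**4. Enrolment period.** March 2022 to November 2024 is 10 + 12 + 11 = 33 months. March to September 2022 is 7 months, in which TBWS and controls had not started. G4H and SPGs were concurrent throughout. Calendar time is otherwise mentioned only through possible COVID-19 effects, to be considered if necessary.

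**5. What could omitting the baseline score cost?** This is illustration only. Let the arms differ by D (in SD) on the outcome at week 1, let r be the correlation between baseline and follow-up, and let both arms regress to a common mean. With no true effect, the spurious difference in change is (1 - r) × D:
- D=0.2, r=0.8: 0.2 × 0.2 = 0.04 SD
- D=0.4, r=0.7: 0.3 × 0.4 = 0.12 SD
- D=0.4, r=0.6: 0.4 × 0.4 = 0.16 SD
- D=0.6, r=0.5: 0.5 × 0.6 = 0.30 SD

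A simulation of a double-robust estimator (155 versus 203 students, D=0.4, true effect 0, 1,000 runs, nominal 5% level) gave:

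| r | Background covariate only: bias, false positives | Baseline score added: bias, false positives |
|---|---|---|
| 0.6 | -0.16 SD, 39% | 0.00 SD, 6.1% |
| 0.7 | -0.12 SD, 28% | 0.00 SD, 4.5% |

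D and r are assumed. The simulation builds in the common mean, so it illustrates the formula and is not separate evidence.

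**The case against.** A reader might infer that baseline loneliness is left out of the selection model. The document does not say so. Table 1 lists a subjective loneliness item among the background variables for all four arms, Strengths and Limitations refers to demographic and baseline data, and nothing excludes week-1 ULS-8 or PHQ-9. A full covariate list may stand in an analysis plan that is not shown. What stands is narrower: the two scales and enrolment period are not named for selection, while baseline symptoms are named for dropout.

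A reader might also infer that the whole adjustment is optional in Statistical Analyses. There the condition attaches to the weighting, and only Strengths and Limitations extends it to the double-robust estimator. It is also fair that weighting chosen on baseline imbalance is not driven by outcomes, and that the authors come close to declaring the condition met. That argues for deleting the condition.

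The strongest objection concerns bias. No baseline outcome scores are given by arm. If arms differ stably in loneliness and do not regress to a common mean, a contrast in change need not be biased, and conditioning on baseline can itself introduce bias. So a claim that results will lean towards G4H, or by how much, is not supported.

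The staggered start is openly disclosed and leaves G4H versus SPGs untouched. Motivation to attend an intervention is largely inapplicable to controls, but that is a reason why the control contrast cannot be guaranteed, not a defence of the guarantee.

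**Conclusion.** The concern holds in two firm parts and one softer part. Firm: the guarantee of unbiased and consistent effects is wrong as stated, whatever an analysis plan adds, and the article contradicts itself on whether the double-robust adjustment is conditional, when its own Table 2 shows differences of up to 0.95 SD between arms. Softer: the selection model should name week-1 ULS-8, PHQ-9 and enrolment period. They are not excluded, but the description as written does not secure them. The account of simultaneous recruitment in the Arm 4 section also conflicts with a 7-month earlier start for G4H and SPGs.

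The 0.04 to 0.30 SD range shows what might be at stake under assumed gaps of 0.2 to 0.6 SD, correlations of 0.5 to 0.8 and regression to a common mean. It is not an estimate of bias in this trial, and its direction cannot be read from the document.

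**What to change.** 1. Replace the guarantee with the assumptions: no unmeasured confounding given the listed covariates, overlap, and at least one correct working model, alongside the stable unit treatment value assumption.
2. Make the double-robust adjustment unconditional and primary for every arm contrast, and use the same wording in Statistical Analyses and in Strengths and Limitations.
3. Include week-1 ULS-8, week-1 PHQ-9 and enrolment period with the background variables in both the propensity and the outcome models.
4. For the contrasts with TBWS and controls, add a sensitivity analysis restricted to students enrolled from October 2022, and correct the Arm 4 section to agree with Setting and Timeline.
5. Add a sensitivity analysis for unmeasured confounding to the control contrast, where motivation is not recorded and readiness only in part.

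The week-1 scores and enrolment dates are already collected, so the cost is plan wording and analysis time. Weighting loses some precision, and the restricted analysis uses fewer G4H students.
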